### Statistical analysis plan

#### Sample size and power calculation

The estimated proportion of diabetic patients 1 year after transplantation is 40% in group 2 (P_2_) and the expected decrease in group 1 (P_1_) is 50% (i.e., 20% at 1 year) [4, 5]. The expected 50% decrease is estimated according to the results obtained with the insulin treatment of Hecking et al. (100% decrease at 1 year) [6]. With the hypotheses H0 (P_2_ − P_1_ = 0; null hypothesis) and H1 (P_2_ − P_1_ ≠ 0; altenative hypothesis) and by considering a group sequential design with a Z score test (pooled estimate for variance estimation), a bilateral alpha risk of 5% and a ß risk of 20%, it will be necessary to randomize 84 patients per group (a total of 168 patients). We expect 10% of patients at 1 year to be non-evaluable and thus we will include 186 patients in total. An interim analysis is planned by the statistician of the investigation team (without the investor being aware of the lifting of the blind) to reject H0 or H1 when at least 84 patients are randomized with one year of follow-up (42 in each group; 50% of the information fraction) using alpha spending function and O’Brien Fleming boundaries. Sample size calculations were performed with the EAST 6 software.

Moreover, as supportive analysis with this sample size will be able to demonstrate an improvement in the time of diabetes-free occurrence from 40% to 20% (hazard ratio of 0.43) with a bilateral alpha risk of 5% and we will have 90% statistical power with 63 events.

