#### Secondary outcome, exploratory, and sensitivity analyses

Selected efficacy analyses will be repeated in the per protocol population (i.e., subset of the ITT population meeting the following criteria: all eligibility criteria fulfilled, at least one dose of allocated treatment administered). The safety population will be used for reporting the safety and treatment exposure data. A modified ITT population will be used for HRQoL analysis, considering all randomized patients with at least the baseline HRQoL questionnaire available. Continuous variables will be summarized using descriptive statistics, i.e., the number of patients with available data (n), mean, median, standard deviation (SD), 25–75% quartile (Q1–Q3), minimum, and maximum. Continuous variables could be transformed to categorical variables using the median or using conventional cut-offs from bibliography or clinical practice. Frequencies in tables will be presented by arm, total frequency, percentages, and missing modality. Qualitative variables will be summarized by means of counts and percentages. Unless otherwise stated, the calculation of proportions will be based on the sample size of the population of interest. The rate of incidence of NODAT will be determined using confidence interval (CI) and compared using Chi 2 test. Univariate and multivariate logistic analyses will be done to identify the independent prognostic factor of the rate of incidence of NODAT and to compute the odds ratio with 95% CI. The continuous variables will be treated as quantitative and qualitative data using cut-offs in anticipation of elaborating a practical clinical tool. Factors will be considered for inclusion in the model if the univariate p value is ≤ 0.1. Interactions between treatment and some variables will be tested at a two-sided 10% level (i.e., a p value > 0.1 indicates no evidence of heterogeneity of treatment effect across the subgroups for each factor). All tests will be performed in an exploratory purpose at a two-sided 5% significance level.

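### The exploratory NODAT logistic analyses use each continuous variable both as measured and cut, with no rule on which coding decides entry at p ≤ 0.1 or goes into the model

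*Protocol article*

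**What the plan says.** All the relevant text is in one section of the protocol article, Secondary outcome, exploratory, and sensitivity analyses.

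- Purpose of the model: "Univariate and multivariate logistic analyses will be done to identify the independent prognostic factor of the rate of incidence of NODAT", with odds ratios and 95% confidence intervals.
- Coding in that model: "The continuous variables will be treated as quantitative and qualitative data using cut-offs in anticipation of elaborating a practical clinical tool". This is worded as a commitment.
- Source of cuts, given earlier among the descriptive summaries and worded as a permission: "Continuous variables could be transformed to categorical variables using the median or using conventional cut-offs from bibliography or clinical practice".
- Entry rule: "Factors will be considered for inclusion in the model if the univariate p value is ≤ 0.1".
- Status: "All tests will be performed in an exploratory purpose at a two-sided 5% significance level".

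The section does not say which coding supplies the p value for the entry rule, or which coding is carried into the multivariable model. It gives no effect size or target power for prognostic factors.

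**The concern.** A variable analysed in two forms yields two p values. If the smaller one can decide entry, the screen is looser than its nominal 10%, and the list of independent factors and their odds ratios will look stronger than the data warrant. If the cut form decides instead, information within each half of the scale is discarded, and true predictors are missed more often.

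The trial has little information to spare. With the planning rates, about 50 patients are expected to have diabetes at one year. The stated reason, a tool for clinical use, concerns how a finished model is presented; it does not require cut variables in screening or estimation. A sample median also shifts from one cohort to the next, so it would make a poor threshold for such a tool.

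**Working it through.** **Inputs from the article (Sample size and power calculation).** 84 evaluable patients per group, 168 in total; diabetes at one year 40% on placebo and 20% on vildagliptin; two-sided 5% alpha; 80% power. Expected events: 84 × 0.40 + 84 × 0.20 = 33.6 + 16.8 = 50.4, or 30% of 168.

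**The plan's own figure.** A fixed-design pooled Z test of 40% against 20% needs 82 per group. The stated 84 fits a small group-sequential inflation, and fixed-design power at 84 per group is 81.3%. The sample size therefore reproduces. The article gives no power or false-entry figure for the prognostic screen, so the rest rests on assumptions.

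**Assumptions.** The predictor is roughly normal, its effect is linear on the log-odds, and the continuous analysis has 80% power.

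**Correlation of the two tests.** For a cut at quantile q, the continuous and cut test statistics have correlation ρ = φ(z_q) / √(q(1 − q)). At the median ρ = 0.3989 / 0.5 = 0.798, so relative efficiency is ρ² = 0.637.

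**Reading A: either coding can trigger entry.** For a factor with no effect, the chance that at least one of the correlated statistics exceeds 1.645 in absolute value is:

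| Codings tried | Chance of passing p ≤ 0.1 |
|---|---|
| Continuous only | 10% |
| Continuous + median | 15.0% |
| Continuous + one cut, 60th to 90th percentile | 15.2% to 17.0% |
| Continuous + median + one further cut, 60th to 90th percentile | 18.6% to 21.8% |

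Simulated logistic regressions (n = 168, 30% events, 6,000 replicates) gave 9.7% for continuous only, 14.7% for continuous or median, 15.2% for continuous or upper quartile, and 19.8% for any of the three.

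As an illustration, assume 15 continuous candidates with no effect. One coding lets in 15 × 0.10 = 1.5 on average; two codings let in 15 × 0.15 = 2.25 to 15 × 0.17 = 2.55.

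**Reading B: the cut coding decides.** Power after cutting is Φ(ρ(z_α + z_power) − z_α), where z_α is the two-sided critical value.

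- Median, α = 0.05: 0.798 × (1.960 + 0.842) − 1.960 = 0.275, so 60.8%, a loss of 19 points.
- Median, α = 0.10: 0.798 × (1.645 + 0.842) − 1.645 = 0.339, so 63.3%, a loss of 17 points.
- Cuts off the median, from the same 80%: 18 to 20 points lost at the 60th percentile, 23 to 26 at the 75th, 37 to 43 at the 90th.

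Simulation (3,000 replicates per slope) agrees in size. At α = 0.10 with slope 0.42 per SD, 77.6% falls to 59.2% at the median cut. At α = 0.05 with slope 0.48 per SD, 78.8% falls to 57.9%.

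**How the readings relate.** Under A the continuous test is still available, so the chance of picking up a true factor cannot fall below that of the continuous analysis alone. Under B there is one test per factor, so double testing does not arise.

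**The case against.** The strongest reply is that little is at stake and that the detail belongs elsewhere. The analyses are labelled exploratory, the primary Z test is untouched, and p ≤ 0.1 is a screening threshold rather than a claimed error rate. The article also says that an analysis plan will be approved before the database is frozen, and the governing coding could be named there. A threshold-shaped effect might even favour a cut. All of this limits the consequence. It does not remove the defect: the article commits to two codings, so an analysis plan that follows it inherits the ambiguity.

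Two stronger readings are tempting, and the text supports neither.

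- A reader might infer that the plan loses power and inflates false entry at once. Each harm needs a different entry rule, and the article states neither rule.
- A reader might extend the point to HbA1c comparisons and to the interaction tests. The general sentence on cutting only says that variables could be transformed. The interaction sentence, "Interactions between treatment and some variables will be tested at a two-sided 10% level", names no continuous variable to be cut. No such analysis is fixed, so power losses there cannot be charged to the plan.

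Nor does the article say that the sample median will be the tool's threshold. The median is only one permitted source of cuts; conventional cut-offs are the other.

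**Conclusion.** The point holds in limited form, as a cheap improvement. The article commits to dual coding in the exploratory NODAT models and leaves open which coding governs entry and modelling.

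One of two costs follows. If either coding can trigger entry, a null factor passes the 10% screen about 15-17% of the time with two codings, or 19-22% with three. If the cut coding governs, power falls by roughly 17 to 19 points from 80% at a median cut, and by more for cuts well away from it.

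These are conditional figures rather than properties of the plan. The power figures need a near-normal predictor, a linear log-odds effect and an assumed 80% starting power. The false-entry figures need the either-coding rule and the same near-normal predictor. The effect is confined to the prognostic model and the tool built on it.

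**What to change.** In Secondary outcome, exploratory, and sensitivity analyses, replace the dual-coding sentence and restrict the general cutting sentence, along these lines: *Each continuous variable will enter the univariate screen and the multivariable NODAT model once, on its measured scale, with a spline or fractional polynomial if linearity is doubtful. Sample-median cuts will not be used for screening or modelling. Pre-specified conventional cut-offs will be applied only after the model is fitted, to present the clinical tool.* The analysis plan should carry the same wording.

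This keeps false entry at the nominal 10% per factor and avoids the loss of power from cutting. It needs no extra data or patients. The small downside is that odds ratios per unit or per SD are slightly less simple to read than a contrast above and below a threshold; presenting the finished model with conventional cut-offs largely covers that.

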### Participants

#### Inclusion criteria

Graft recipients aged 18 or above will be eligible for inclusion if they:Receive a first kidney transplantAre considered at high risk of developing NODAT, having at least two of the three following criteria: age > 50 years; body mass index (BMI) > 30 kg/m^2^; direct family history of type 2 diabetesCan receive immunosuppressive therapy including tacrolimus, mycophenolic acid, and steroidsAre patients in whom the cessation of steroids may be considered at the latest 3 months post-transplantSign the informed consent for study participationAre affiliated with a medical care system

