#### Randomization

Patients will be randomized 1:1 into two groups using a minimization technique with stratification according to center and the number of risk factors for developing diabetes (two or three).Group 1 (interventional group) will be treated with vildagliptin 100 or 50 mg/day for 2 months (depending on whether their glomerular filtration rate is above or below 50 ml/min; Modification of Diet in Renal Disease (MDRD) equation).Group 2 (placebo group) will be treated with placebo according to the same dosage.

Random allocation sequence is generated using CleanWeb™. The minimization algorithm takes into account already randomized patients in order to allocate a new treatment to minimize difference between stratification criteria. The randomization result provided by the system is attributed in 80% of cases; otherwise, the other treatment is attributed. Neither the nurse nor the doctor nor the patient will know the nature of the ingested tablets. The blinding is created by the clinical research associate coordinator. The randomization number is assigned directly to the centers via CleanWeb™.

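### Enrolling on at least two of three risk factors ties those factors together negatively, so the univariate p ≤ 0.1 screen can hide a truly prognostic eligibility factor or reverse its sign in the exploratory NODAT model

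*Protocol article*

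**What the plan says.** Under Inclusion criteria, the protocol article admits patients "having at least two of the three following criteria: age > 50 years; body mass index (BMI) > 30 kg/m^2^; direct family history" (the third criterion concerns diabetes of type 2). Under Randomization, the minimisation uses centre and whether a patient has two or all three of these factors.

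Under Secondary outcome, exploratory, and sensitivity analyses, univariate and multivariate logistic regressions are planned "to identify the independent prognostic factor of the rate of incidence of NODAT". Entry to the multivariate model is governed by one rule: "Factors will be considered for inclusion in the model if the univariate p value is ≤ 0.1". No exception is made for the three eligibility factors. On coding, the same section says: "The continuous variables will be treated as quantitative and qualitative data using cut-offs in anticipation of elaborating a practical clinical tool". It describes the tests as exploratory.

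**The concern.** The multivariate model is meant to find independent predictors, but the gate in front of it looks at each factor alone. Under this eligibility rule, a patient who lacks one factor must have both others. A univariate contrast on age therefore compares patients over 50 who have one or both of the other factors with patients of 50 or under who have both. The comparison group is loaded with the other risk factors by design.

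The multivariate model could separate the three effects, but the gate acts first. A real predictor may be lost before adjustment, or a factor may be carried forward with a misleading univariate OR. The stated aim includes a clinical tool, so the choice of variables matters beyond a descriptive table.

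**Working it through.** **Inputs from the article.** Eligibility requires at least two of three factors. The gate is univariate p ≤ 0.1. There are 168 evaluable patients (84 per group). "The estimated proportion of diabetic patients 1 year after transplantation is 40% in group 2" and 20% is expected in group 1, so the pooled rate is (40% + 20%)/2 = 30%, or 0.30 × 168 ≈ 50 events. The 168 is credible: a fixed-design pooled Z test for 40% against 20% needs 82 per group, and one interim look accounts for the small excess. The article gives no figure for how the gate performs.

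**Inputs assumed.** Prevalences of age/BMI/family history before selection are set A 60/20/30% or set B 50/25/35%, independent before selection. True ORs are varied. The article's only effect size is a 20-fold risk for age over 55 with BMI over 30 (Conditions for patient selection). Split equally and multiplicatively, that is √20 ≈ 4.5 each, which is also an assumption.

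**Step 1: sign of the dependence (needs no assumed figure).** Nobody lacks both A and B, so P(A=0, B=0) = 0 and

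cov(A,B) = 0 − P(A=0)·P(B=0) < 0

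whenever each factor is absent in some patients. This is exact at the eligibility cut-offs. In set A the patterns have weights:
- age+BMI: 0.6×0.2×0.7 = 0.084
- age+family history: 0.6×0.8×0.3 = 0.144
- BMI+family history: 0.4×0.2×0.3 = 0.024
- all three: 0.6×0.2×0.3 = 0.036

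The sum is 0.288, so the shares are 29.2%, 50.0%, 8.3% and 12.5%.

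**Step 2: one univariate OR by hand (set A, all true ORs 2).** With the mean risk fixed at 30%, each two-factor pattern has risk 28.0% and the three-factor pattern 43.8%.
- Age present (91.7%, 154 patients): (0.792×0.280 + 0.125×0.438)/0.917 = 30.2%.
- Age absent (8.3%, 14 patients): 28.0%.
- OR = (0.302/0.698)/(0.280/0.720) = 1.11.
- SE of log OR = √[1/(154×0.302×0.698) + 1/(14×0.280×0.720)] = 0.62.
- Chance of p ≤ 0.1 = Φ(0.104/0.62 − 1.645) + Φ(−0.104/0.62 − 1.645) ≈ 10%.

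**Step 3: all cases** (univariate OR and chance of passing; sets A and B).

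| True ORs, age/BMI/family history | Age | BMI | Family history |
|---|---|---|---|
| 2/2/2 | 1.11-1.14; 10-11% | 1.21-1.22; 15% | 1.14-1.16; 12-13% |
| 3/3/3 | 1.19-1.24; 11-13% | 1.36-1.37; 23-24% | 1.25-1.28; 16-17% |
| 4.5/4.5/2 | 1.67-1.77; 20-29% | 2.27-2.40; 74-81% | 0.62-0.64; 33-38% |
| 4.5/4.5/1 | 2.20-2.31; 29-43% | 3.25-3.65; 93-97% | 0.31-0.33; 92-94% |

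The reversal can be seen directly in set A, third row. Patients without family history all have age and BMI, with risk 37.5%. Those with it average (0.583×0.210 + 0.125×0.545)/0.708 = 26.9%. The OR is about 0.62 although the true OR is 2.

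**Step 4: how much is due to selection?** A simulation used wider prevalences (age 50-70%, BMI 20-40%, family history 25-40%) and the planned treatment effect. Pass rates were 10-18% at OR 2 and 8-31% at OR 3. With the same marginal frequencies but independent factors they were 23-60% and 42-91%. At OR 1.5 the comparison is 9-13% against 15-33%, so low power explains part of the loss there.

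**Step 5: continuous age and BMI.** The dependence weakens: the age-BMI correlation is −0.15 to −0.19, against −0.30 (A) and −0.36 (B) when both are dichotomised. At OR 1.3-1.5 per 10 years and per 5 kg/m², age passes 28-47% and BMI 19-32%. At OR 2 per unit, age passes 82-88% and BMI 53-77%. Family history, with true OR 1.5-3, passes only 10-19% throughout.

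**The case against.** A reader might infer that the gate will usually discard all three factors, and that the trial would then contradict its own basis for selection. The documents do not support that.

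- It needs roughly equal effects and dichotomised coding. With unequal effects the strongest factor tends to survive: BMI passes 66-70% at true ORs 2/3/1.5 and 74-81% at 4.5/4.5/2.
- The article also analyses continuous variables as quantitative data, where a strong age or BMI effect usually passes.
- Prevalences and effect sizes are not given.
- The selection criteria rest on external data. A null result among patients who all have at least two factors would not contradict those data.

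The strongest further objection is that the trial could barely detect these factors anyway. With all three dichotomised factors forced in, approximate power at p < 0.05 is 15-30% per factor at OR 2 and 31-62% at OR 3 (sets A and B). This stands, and it limits what the fix can deliver. It does not defend the gate, which adds a directional distortion to low power.

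It can also be said that the analysis is exploratory, that the wording speaks only of consideration for entry, and that an analysis plan will follow. The first point limits the consequence. The other two do not remove the problem, because the article already fixes the screening criterion and exempts no factor.

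**Conclusion.** The concern holds in a limited form. The negative dependence at the eligibility cut-offs follows from the inclusion rule alone. A univariate p ≤ 0.1 gate is therefore a poor entry test for these three factors: it can mask a real effect or reverse its sign. Under the assumed prevalences, 168 patients and 30% events, equal true ORs of 2-3 shrink to 1.11-1.37 and pass 10-24% of the time. With strong age and BMI effects, a family history OR of 2 appears as 0.62-0.64, and a family history with no effect passes 92-94% of the time as falsely protective.

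These sizes are illustrations. They depend on assumed prevalences, independence before selection and effect sizes, and they shrink for age and BMI kept continuous. The primary comparison, its alpha and the sample size are untouched.

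**What to change.** In the exploratory NODAT model:

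1. Enter age and BMI (both continuous), family history (yes/no) and treatment arm regardless of univariate p.
2. Screen any other candidate adjusted for these four terms, not alone.
3. State that any resulting tool applies only to patients with at least two of the three factors.
4. State that a non-significant eligibility factor will be reported with its OR and confidence interval, and not described as not prognostic.

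The cost is wording only, since eligibility and randomization already require these variables. The downside is four degrees of freedom fixed in advance with about 50 events, which leaves room for fewer other candidates. If the three factors are also fitted at their eligibility cut-offs, the two-or-three stratification indicator cannot be added, because it equals their sum minus two.

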##### Health-related quality of life

The minimal clinically important difference will be fixed to 10 points for each HRQoL score. A descriptive analysis of the scores obtained for each questionnaire at baseline and at each follow-up will be performed using n, mean (SD), and median (range) for all patients and according to the treatment arm. A linear mixed model for repeated measure will be applied to HRQoL scores integrating all measurement times, including a treatment effect, a time effect, and an interaction between time and treatment. The time to HRQoL score deterioration (TTD) approach will also be explored. The TTD will be defined as the time from inclusion in the study to the first deterioration of at least 10 points of the HRQoL score compared to the baseline score [13, 14]. The TTD will be determined according to the Kaplan-Meier estimation method and compared by treatment arm using the Log-rank test. Univariate and multivariate Cox regression models will be performed in order to estimate hazard ratio with 95% CI to investigate potential factors independently associated with the TDD.

All tests in HRQoL analyses will be performed at a two-sided 1% significance level to prevent inflation of the alpha type one error with a Bonferroni approach for the five targeted dimensions (5%/5 = 1%; physical health, mental health, medical care and satisfaction, treatment, and fear of losing the graft).

The EQ-5D questionnaire is a standardized tool consisting of five dimensions: mobility, self-care, usual activity, pain and discomfort, and anxiety and/or depression. Each patient’s quality-adjusted life year will be calculated, from D0 until M12 or censoring date, by multiplying the duration of each period by the corresponding period’s utility score.

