### Interventions

#### Timing of administration of the study treatment

First administration of the study treatment (vildagliptin or placebo) will be performed within hours prior to patient departure to the operating room. The dosage of vildagliptin will conform to the marketing authorization of data in its indication in the treatment of diabetes in kidney transplant patients. Patients will receive a half dose of therapy until they have a glomerular filtration rate greater than 50 ml/min of (MDRD equation). Patients will receive one oral tablet in the morning and one in the evening (100 mg per day) or just one in the morning (50 mg per day) for 2 months.

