### Study outcomes

The primary endpoint is the proportion of diabetic patients 1 year after transplantation, defined as one of the following criteria: patients receiving a diabetic treatment, patients have a fasting glucose above 7 mmol/l, and/or patients with an abnormal oral glucose tolerance test (OGTT).

The criteria for secondary assessments are: glycated hemoglobin (HbA1c) 3 months, 6 months, and 12 months after transplantation; occurrences of acute rejection, infection, graft loss, and patient death 3, 6, and 12 months after transplantation; clinical history (cardiovascular history, baseline renal disease, dialysis, anti-human leukocyte antigen antibodies, dyslipidemia, hypertension, type of donor, duration of ischemia, cytomegalovirus (CMV) status, CMV prophylaxis, pneumocystis prophylaxis); biological data (creatinine, uric acid, C reactive protein (CRP), blood sugar balance, lipid profile, liver function tests, pancreatic balance, and blood counts); health-related quality of life (HRQoL; Renal Transplant Quality of Life (ReTransQoL) questionnaire), 8 days and 3, 6, and 12 months after transplantation; and the cost-effectiveness of prevention of diabetes with vildagliptin correlated to outcomes.

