### Health-related quality of life, renal transplantation, and diabetes

The HRQoL assessment significantly predicts patient survival, particularly in patients with chronic kidney disease [18, 19]. Moreover, as transplantation results in one of the best increases of patients’ quality of life, its estimate is essential in the treatment evaluation of this population [15, 20–22]. It has been shown that cardiovascular complications, dialysis method, hypertension, method of diabetes treatments (oral or injectable), and hypoglycemia influence the quality of life [19, 23, 24]. Furthermore, in patients with type II diabetes, hypoglycemia is associated with depressive symptoms and heightened anxiety and other factors important for quality of life [25]. Prospective reports have indicated that diminished HRQoL among adults with type II diabetes is associated with subsequent mortality risk [26]. Kizilisik et al. [27] have demonstrated in a cohort of 86 kidney transplant patients that transplantation and diabetes have direct, opposite, and independent effects on the quality of life of patients.

Although the most common questionnaire used for assessing HRQoL is the Short Form 36 (SF-36), Gentile et al. [28] have developed a quality of life questionnaire to specifically assess the quality of life associated with renal transplantation in France. This questionnaire was analyzed, evaluated, and validated by French public health priorities [29]. That is why the HRQoL questionnaire ReTransQoL will be used in our study [28, 30]. The ReTransQOL questionnaire was completed at t0, 8 days, 3 months, 6 months, and 12 months after transplantation. The questionnaire is done on day 0 and day 8 for two reasons: to get rid of the beneficial effect on patient’s quality of life due to transplant announcement and to overcome the impossibility of filling out the form just before entering the operative block. The EQ-5D questionnaire allows evaluation of a wide variety of interventions. It is widely used in utility calculations. It has evidence of validation in type 2 diabetes with a variety of different profiles (treatment, symptoms, and complications) [31].

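### The HRQoL mixed model treats baseline as an outcome with a free treatment difference and does not adjust for it, which costs precision, not validity

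*Protocol article*

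**What the plan says.** The statistical subsection on health-related quality of life states which scores are modelled: "A linear mixed model for repeated measure will be applied to HRQoL scores integrating all measurement times". The terms of that model are then given as "including a treatment effect, a time effect, and an interaction between time and treatment". It mentions neither a baseline covariate nor a common baseline mean. The same subsection sets 10 points as the minimal important difference and divides the level over five dimensions: "All tests in HRQoL analyses will be performed at a two-sided 1% significance level".

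The HRQoL analysis set is defined under Secondary outcome, exploratory, and sensitivity analyses as "considering all randomized patients with at least the baseline HRQoL questionnaire available". Every analysed patient therefore has a score called baseline.

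The article is less clear on when that score is taken:
- The discussion section on HRQoL includes a time-zero form: "The ReTransQOL questionnaire was completed at t0, 8 days, 3 months, 6 months, and 12 months after transplantation".
- Study outcomes lists only "8 days and 3, 6, and 12 months after transplantation".
- The discussion explains the pair of D0 and D8 forms partly as a way "to overcome the impossibility of filling out the form just before entering the operative block".
- Under Timing of administration, the first dose "will be performed within hours prior to patient departure to the operating room".

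**The concern.** Allocation is randomized 1:1, so the arms have equal expected scores on any questionnaire completed before the first dose. A model with treatment, time and their interaction, and with baseline among the outcomes, still estimates a separate baseline mean for each arm. With complete data and visit as a category, it then takes no strength from the baseline score. The interaction contrast is the plain difference in mean change, and the treatment difference at M12 is the plain difference in M12 means. Adjusting for baseline beats both.

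The treatment main effect is also awkward to read. Depending on the coding, it is the D0 difference itself or an average that includes D0.

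The trial is sized for the diabetes endpoint, and the HRQoL tests run at 1%. Precision could therefore affect whether a relevant HRQoL difference is detected.

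**Working it through.** **The plan's own figures.** The HRQoL level reproduces: 5%/5 = 1%. The article gives no SD, correlation, sample size or power for HRQoL, so there is no HRQoL power figure to reproduce.

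**Inputs from the article.** Two-sided 1% level; 10 points; 84 per arm (Sample size and power calculation, for the primary endpoint); visits D0, D8, M3, M6 and M12.

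**Assumptions.** Correlation r between D0 and M12 of 0.3, 0.5 or 0.7; equal SD at both visits, 20 or 25 points; 84 per arm with complete HRQoL data; 10 points taken as the true between-arm mean difference at M12.

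**Variances.** With visit as a category and complete data, in units of SD² × 2/n:
- Written model, change from D0 to M12: 2(1 − r)
- Written model, treatment difference at M12: 1
- Common D0 mean, or D0 as covariate: 1 − r²

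The proportional saving is 1 − (1 − r²)/[2(1 − r)] = (1 − r)/2 against the change contrast, and 1 − (1 − r²)/1 = r² against the M12 difference.

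| r | Change | M12 difference | Adjusted | Saving vs change | Saving vs M12 difference |
|---|---|---|---|---|---|
| 0.3 | 1.40 | 1.00 | 0.91 | 35% | 9% |
| 0.5 | 1.00 | 1.00 | 0.75 | 25% | 25% |
| 0.7 | 0.60 | 1.00 | 0.51 | 15% | 49% |

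**Check of the algebra.** Generalised least squares with five visits and 84 per arm, under compound symmetry at r = 0.5, gives 0.02381 for the written model's change contrast: (2/84) × 1.00 = 0.02381. With a common D0 mean it gives 0.01786: (2/84) × 0.75 = 0.01786. The match also holds under a decaying correlation. A simulation of 20,000 trials at r = 0.5 gave a change-to-adjusted variance ratio of 1.34, against 1/0.75 = 1.33 expected.

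**Power.** Power = Φ(10/SE − 2.576), with SE = SD × √(2V/84) and V from the table. Example for SD 20, r = 0.3, change: SE = 20 × √(2 × 1.40/84) = 3.65, and Φ(2.74 − 2.576) = 56%.

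| SD | r | Change | M12 difference | Adjusted |
|---|---|---|---|---|
| 20 | 0.3 | 56% | 75% | 79% |
| 20 | 0.5 | 75% | 75% | 88% |
| 20 | 0.7 | 95% | 75% | 98% |
| 25 | 0.3 | 35% | 51% | 56% |
| 25 | 0.5 | 51% | 51% | 66% |
| 25 | 0.7 | 78% | 51% | 85% |

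**If time is linear.** Under compound symmetry, the variance of the treatment-by-time slope in the written model is 1.29, 1.15 and 1.07 times that of the common-baseline model at r = 0.3, 0.5 and 0.7. The loss is smaller but in the same direction.

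**The case against.** **The model is standard and valid.** This stands. A reader might infer that the free baseline difference biases the HRQoL result or inflates its type I error. It does neither.

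**The contrast is not named.** This also stands. A reader might take 35%, 25% and 15% as the loss, but those figures hold only if change from D0 is tested. The same model also yields the M12 difference, for which the saving at r = 0.3 is only 9%, though at r = 0.7 it is 49%. The article does not state the covariance structure or the coding of time either.

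**The detail belongs in the later plan.** The Statistical analysis section does promise an HRQoL analysis plan before the database is frozen. The article nevertheless commits to outcome times and model terms, and a plan that follows them literally inherits the loss. The list of terms does not rule out adding a baseline term, so the amendment is easy.

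**A clean baseline is not secure.** This is the strongest objection, and it limits the remedy. If the form called baseline is completed after the first dose, randomization no longer guarantees equal means. Forcing them equal could introduce bias that the written model avoids.

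**The 10 points may not be a between-arm target.** The article fixes it as the minimal important difference and applies it explicitly to deterioration within a patient. Its use in the power figures above is an assumption.

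**Conclusion.** The point holds as one of efficiency on a secondary outcome; the primary analysis is untouched. For 0 < r < 1, a baseline-adjusted or common-baseline model is more precise than either natural contrast from the written model, given categorical time and complete data. The variance reduction forgone is (1 − r)/2 for change from D0 and r² for the M12 difference. Even against the better of the two contrasts it is 9%, 25% and 15% at r = 0.3, 0.5 and 0.7. With missing visits these figures are approximate.

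The power figures are illustrations under assumed SD, r, n and effect, and no HRQoL power claim in the article fails. The gain is available only if a score is taken before the first dose, which the article leaves unsettled.

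A reader might also expect a common-baseline model to bring in patients without a D0 form. The stated analysis set excludes them, so that would follow only if the set were changed too.

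**What to change.** 1. Reconcile Study outcomes with the discussion section on HRQoL. State whether a D0 questionnaire is completed before the first dose, and which score is the baseline.
2. If a pre-dose D0 score exists, either keep all times in the response with a common D0 mean for the two arms and treatment terms only at D8, M3, M6 and M12, or enter the D0 score as a covariate with those four visits as outcomes.
3. Name the treatment difference at M12 as the tested contrast.
4. Keep D8 as a follow-up outcome, since it comes after the first dose. Do not apply the common-mean constraint to any post-dose score. If there is no pre-dose score, keep the unconstrained model and name its contrast.

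The cost is a clarification of the visit schedule and a short change to the HRQoL model text, made before that plan is approved. If pre-dose forms are already being collected, no new data are needed.
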